## Abstract

**Background:**

Cognitive problems frequently occur in patients with multiple sclerosis (MS) and profoundly affect their quality of life. So far, the best cognitive treatment options for MS patients are a matter of debate. Therefore, this study aims to investigate the effectiveness of two promising non-pharmacological treatments: cognitive rehabilitation therapy (CRT) and mindfulness-based cognitive therapy (MBCT). Furthermore, this study aims to gain additional knowledge about the aetiology of cognitive problems among MS patients, since this may help to develop and guide effective cognitive treatments.

**Methods/design:**

In a dual-centre, single-blind randomised controlled trial (RCT), 120 MS patients will be randomised into one of three parallel groups: CRT, MBCT or enhanced treatment as usual (ETAU). Both CRT and MBCT consist of a structured 9-week program. ETAU consists of one appointment with an MS specialist nurse. Measurements will be performed at baseline, post-intervention and 6 months after the interventions. The primary outcome measure is the level of subjective cognitive complaints. Secondary outcome measures are objective cognitive function, functional brain network measures (using magnetoencephalography), psychological symptoms, well-being, quality of life and daily life functioning.

**Discussion:**

To our knowledge, this will be the first RCT that investigates the effect of MBCT on cognitive function among MS patients. In addition, studying the effect of CRT on cognitive function may provide direction to the contradictory evidence that is currently available. This study will also provide information on changes in functional brain networks in relation to cognitive function. To conclude, this study may help to understand and treat cognitive problems among MS patients.

**Trial registration:**

This trial was prospectively registered at the Dutch Trial Registration (number NTR6459, registered on 31 May 2017).

## Background

Multiple sclerosis (MS) is a chronic disease of the central nervous system, which leads to physical, neuropsychiatric and cognitive problems. Cognitive problems are commonly reported by MS patients, with prevalence rates of objective cognitive deficits varying between 43 and 70% [1]. The most frequently affected cognitive domains are information processing speed, memory, attention, visuospatial processing and executive function. These objective cognitive deficits (i.e. assessed with cognitive tests) only show a weak relation with the cognitive complaints reported by MS patients themselves [2, 3]. Despite this weak relation, subjectively experienced cognitive problems are arguably as important as objective cognitive deficits, since they may reflect the burden of cognitive problems in daily life.

The impact of cognitive problems on daily life can be extensive given the relatively young age of disease onset. Problems in social relations and work participation are likely to occur, consequently negatively affecting the quality of life of MS patients [1, 4]. This highlights the need for effective cognitive treatment options for MS patients. To develop and guide effective cognitive treatments, knowledge about the aetiology of objective and subjective cognitive problems is essential.

### Aetiology of cognitive problems

The aetiology of objective and subjective cognitive problems in MS is complex and not completely understood. Objective cognitive deficits in MS patients have been linked to cortical, deep grey matter and white matter damage [5, 6]. Researchers have argued that this widespread pathology may result in a disruption of the connectivity between brain regions, which in turn may result in cognitive decline [7]. Changes in brain networks are indeed present in MS patients: studies have reported changes in functional connectivity [7] and a loss of hierarchal structure [8], which both related to reduced objective cognitive performance in MS patients.

Whereas the aetiology of objective cognitive deficits is widely studied, studies focusing on the aetiology of subjective cognitive complaints are rare. Since subjective and objective cognitive problems correlate weakly [2, 3], their aetiology might be different [9]. One recent study found that subjectively experienced cognitive problems could not be explained by brain pathology, but no measures of brain networks were included [9]. To date, the study of brain networks and their relation to objective and subjective cognitive function among MS patients is still in its infancy. Additional well-designed studies are needed to unravel the aetiology of objective and subjective cognitive problems in MS.

### Treatment of cognitive problems

The best cognitive treatment options for MS patients are still a matter of debate [10]. A promising non-pharmacological treatment option is cognitive rehabilitation therapy (CRT) [10]. CRT entails the learning of new cognitive strategies aimed at compensating for cognitive problems. The use of these strategies shows positive effects on cognitive function among stroke and brain injury patients [11]. There is also some evidence for positive effects of CRT on cognitive function among MS patients. However, no final conclusion on the effectiveness of CRT can be established due to contradictory findings [12, 13]. These contradictory findings may be explained by small sample sizes, heterogeneous interventions across studies and methodological limitations (e.g. biased selection) [12, 13].

A second promising non-pharmacological treatment option is mindfulness-based cognitive therapy (MBCT) [14]. MBCT entails mindfulness training combined with elements of cognitive behavioural therapy. There is preliminary evidence that mindfulness-based interventions positively affect cognitive function in healthy individuals [14, 15] and they may even influence brain structures and functions that are involved in cognitive function [14, 16, 17]. In MS patients, positive effects of mindfulness-based interventions on psychological symptoms have been found [18–20], and a recent pilot study reported some positive effects of mindfulness on objective cognitive function [19]. To our knowledge, no other studies have investigated the effect of mindfulness-based interventions on cognitive function among MS patients. In summary, well-designed studies are necessary to investigate the effect of MBCT and CRT on cognitive function among patients with MS.

### The REMIND-MS study

The REMIND-MS study is a randomised controlled trial (RCT) that investigates the effect of CRT and MBCT on subjective and objective cognitive function in MS patients. Additionally, resting-state magnetoencephalography (MEG) data will be obtained to gain additional knowledge about the aetiology of subjective and objective cognitive problems with respect to functional brain networks, and to unravel if cognitive improvements after both interventions are associated with functional brain network changes.

### Objectives

This study primarily aims to examine the effectiveness of CRT and MBCT on subjectively experienced cognitive problems among MS patients. We hypothesise that both CRT and MBCT positively affect subjective cognitive function compared to enhanced treatment as usual (ETAU). We also expect positive effects on the secondary outcome measures objective cognitive function, functional brain network measures, psychological symptoms, well-being, quality of life and daily life functioning. Additionally, we will evaluate in an exploratory way whether there are differences in intervention effects between CRT and MBCT.

Secondary study objectives are:to explore the role of functional brain network measures (using MEG) in subjective and objective cognitive problems, and to evaluate whether there are differences in functional brain network measures between these types of cognitive problems;to explore the role of functional brain network measures as possible mediators in the effect of the interventions;to evaluate whether alterations in objective cognitive function, functional brain network measures, psychological symptoms, well-being, quality of life and daily life functioning are mediating factors that determine subjective cognitive function;to evaluate which factors determine whether a patient is likely to benefit from one of the therapies, such disease severity, severity of cognitive problems and mood at baseline, or gender.

## Methods-design

### Design

The REMIND-MS study is a dual-centre, single-blind RCT with three parallel groups: CRT, MBCT and ETAU. All interventions last nine weeks in total. Measurements take place at baseline, post-intervention and after a 6-month follow-up period. The full trial design is summarised in Fig. 1.

**Fig. 1 Fig1:**
[figure not shown]
Flowchart of the trial design. KR = Klimmendaal Rehabilitation Center; VUmc = VU University Medical Center

### Setting

Selection and measurements take place at the VU University Medical Center in Amsterdam, the Netherlands. Part of the measurements, that is, the self-report questionnaires, can be completed by the participants at home. The interventions take place at two centres in the Netherlands: VU University Medical Center in Amsterdam and Klimmendaal Rehabilitation Center in Arnhem.

### Participants

#### Recruitment and consent

Participants are recruited through the participating centres (VU University Medical Center and Klimmendaal Rehabilitation Center), the ‘VUmc MS Center Amsterdam’ website and MS patient associations. All potentially eligible participants who express interest in the study are provided with written trial information, which contains information about the rationale, purpose and personal implications of the study. The information sheet also includes contact details of the trial coordinator and of an independent medical doctor who is not part of the research team, who can both be contacted for additional information. After sufficient time for consideration, potential participants who are still interested to participate are invited by the trial coordinator to sign the informed consent form. After signing the informed consent form, it will be checked whether the participants are fully eligible.

On the informed consent form, participants have the option to give permission for an informant to be contacted. If permission is given, an informant of the participants will also receive written information and an informed consent form, as informants will be asked to complete one questionnaire at three time-points (see outcome measures). On the informed consent form, participants and their informants also have the option to give permission for using their data for other research, for sharing their data with researchers outside of the European Union and to be contacted again for follow-up research.

#### Inclusion criteria

Participants are eligible to participate if they meet the following criteria: (1) between 18 and 65 years of age, (2) confirmed diagnosis of MS according to the McDonald 2010 criteria [21], (3) a minimum score of 23 on the Multiple Sclerosis Neuropsychological Questionnaire – Patient version (MSNQ-P), which measures subjective cognitive complaints [22].

#### Exclusion criteria

Participants who meet any of the following criteria are excluded from participation: (1) psychosis, (2) suicidal ideation, (3) an inability to speak or read Dutch, (4) previous experience with a similar intervention (e.g. a comparable cognitive rehabilitation training or mindfulness training), (5) physical or cognitive disabilities, comorbidities or treatments that would interfere too much with the interventions to enrol in this study (to be evaluated on an individual level). The reasons for excluding participants who express interest in the study will be accurately documented.

#### Sample size calculation

Mixed model analyses will be applied with three measurements comparing two groups (MBCT vs. ETAU, CRT vs. ETAU). There are no previous studies with MS patients that investigated the effect of CRT or MBCT on the primary outcome measure, the Cognitive Failure Questionnaire (CFQ) [23]. Based on a previous RCT using a comparable outcome measure, a medium effect size can be expected [24, 25]. With an alpha of .05, a power of .80, an intra-class correlation of .06, and 33 participants per group, a minimal difference of 0.62 SD can be detected between two groups. Taking into account drop-out and loss to follow-up, we intend to recruit 40 MS patients per group.

### Interventions

All interventions last nine weeks. The CRT consists of nine 2.5-h group sessions, MBCT of eight 2.5-h group sessions and one ‘silent day’, and enhanced treatment as usual (ETAU) of one individual appointment within the 9-week period. For CRT and MBCT, the optimal group size was determined based on previous experiences. Groups will consist of a maximum of 6 people in the CRT group and a maximum of 10 people in the MBCT group. Professionally trained psychologists will guide the CRT sessions, certified mindfulness trainers will teach the MBCT sessions and MS specialist nurses will have appointments with participants from the ETAU group. All trainers will be instructed and supervised by the same specialists. The interventions will be provided in a standardised manner using a written protocol. The trainers are instructed not to disclose treatment information to trainers from another treatment arm. All participants will receive an information brochure on MS and cognition.

#### Cognitive rehabilitation therapy (CRT)

The CRT protocol focuses on the following cognitive domains: speed of information processing, memory, executive function and mental fatigue. Cognitive impairments will be treated by a combination of compensatory strategy training and psycho-education. The proposed strategies are based on MS-tailored variants of evidence-based treatments that have been developed in CRT research with brain-injured subjects. Treatment of problems in information processing speed will be based on ‘Time Pressure Management’ [26, 27], memory on ‘Training Memory strategies’ [28], executive function on a ‘Multifaceted Treatment for Executive Dysfunction’ [29, 30] and mental fatigue on ‘Cognitive and Graded Activity Training’ [31, 32]. These four treatments are incorporated in the protocol as described by Geusgens, Baars-Elsinga, Visser-Meily and van Heugten [33]. In addition to cognitive strategy training, CRT focuses on emotional and behavioural changes, and grief resolution. Grief resolution will be included by explaining the stages of bereavement and by discussing the loss of physical independence, mobility, cognitive ability and emotional control on self-esteem and future perspective. The participants will receive homework assignments aimed at identifying their own cognitive problems and at applying the learned strategies in daily life situation. These homework assignments will take 30 to 45 min a day, 6 days per week.

#### Mindfulness based cognitive therapy (MBCT)

The MBCT protocol is primarily based on the MBCT program by Segal, Williams and Teasdale [34]. MBCT is an intervention in which aspects of mindfulness meditation are combined with aspects of cognitive behavioural therapy. MBCT focuses on increasing awareness of the present moment. To achieve this, participants will be trained in both self-regulation of attention and non-judgmental awareness of moment-to-moment experience. Patients will become more aware of their emotions, thoughts and behaviours and will learn to use more adaptive behaviour to respond to their symptoms. The program will be adapted to the MS patients in terms of tailoring psycho-educative elements to themes relevant to the MS patient (e.g. cognitive problems) and modified movement exercises (for patients suffering from physical impairments). Participants will receive guided mindfulness meditation exercises of 30 to 45 min, 6 days per week, for home practice and a reader with home practice instructions and background information. All therapists will fulfil the advanced criteria of the Association of Mindfulness Based Teachers in the Netherlands and Flanders, which are in concordance with those of the UK Mindfulness-Based Teacher Trainer Network [35].

#### Enhanced treatment as usual (ETAU)

Enhanced treatment as usual (ETAU) entails an appointment with an MS specialist nurse in addition to usual care. The appointment will focus on psycho-education. More specifically, the MS specialist nurse will provide the participants with information on the frequently affected cognitive domains in MS and their relation to brain pathology. This will occur in a standardised manner.

#### Teacher ratings

CRT and MBCT sessions will be recorded on video to evaluate teacher competence and protocol adherence. These video recordings will solely be used for the purpose of trainer evaluation, and the camera will be directed at the trainer. For the CRT sessions, adherence to the protocol will be checked using a checklist. For the MBCT sessions, the Mindfulness-Based Interventions - Teachers Assessment Criteria [36] will be used.

#### Adherence

For all groups, attendance to the sessions will be documented. For the CRT group, adherence to homework assignments will be checked and evaluated during each visit of the treatment period. For the MBCT group, adherence will be assessed during the entire treatment period with a calendar on which participants fill out whether they adhere to both formal (e.g. the sitting meditation) and informal (e.g. 3-min breathing space) mindfulness exercises.

#### Replacement and follow-up of withdrawn participants

Participants can leave the study at any time for any reason without any consequences. Follow-up measurements will still be scheduled if the participant is willing and able to participate in follow-up measurements. There will be no replacement of individual participants after withdrawal. If a high rate of participants drops out during the study, more participants will be included in the study. These participants will be randomly allocated to one of three parallel groups using the randomisation and minimisation procedure as described under ‘randomisation and blinding’.

#### Relevant concomitant care and interventions

During the intervention period and the 6-months follow-up period, patients are asked not to follow an intervention outside this study that focuses on mindfulness or cognition, and to keep their level of care constant during this period when possible. Naturally, usual care should continue, as do new treatment options when the health situation of the patient changes.

### Demographic and patient characteristics

At baseline, the following demographic characteristics are collected: age, gender, work status and education. In addition, the following clinical characteristics will be noted: comorbid condition as defined by the Cumulative Illness Rating Scale (CIRS) [37], subtype of MS, year of diagnosis, disease duration and MS disability as defined by the Expanded Disability Status Scale (EDSS) [38]. If an EDSS score is not available, or if this score has been determined more than three months ago, a new EDSS score will be gathered at baseline. The use of medication will be noted at each assessment. Health care consumption will be measured with a questionnaire on healthcare utilisation and productivity losses in patients with a psychiatric disorder (TIC-P) [39] and will be administered at each measurement. Table 1 presents an overview of the demographic and patient characteristics that will be collected at each assessment.

**Table 1 Tab1:** Overview of outcome measures per assessment

Assessment	Baseline	Post-intervention	Follow-up
Demographic characteristics	X		
Medical history (e.g. MS subtype)	X		
Use of medication	X	X	X
Expanded Disability Status Scale (EDSS)	X		
Health care consumption	X	X	X
Questionnaires measuring subjective cognitive complaints, psychological symptoms, quality of life, well-being and daily life functioning	X	X	X
Neuropsychological assessment	X	X	X
Magnetoencephalography (MEG)	X	X	X
Qualitative data to improve the interventions		X	

### Outcome measures

All outcome measures will be administered at each assessment: at baseline, post-intervention and 6-months follow-up (see Table 1).

#### Primary outcome measure

The primary outcome measure is the level of subjective cognitive complaints and is measured with the CFQ [23]. Subjective cognitive complaints in terms of executive function will be measured with the Behaviour Rating Inventory of Executive Function – Adult Version (BRIEF-A) [40]. The BRIEF-A consists of a self- and an informant report version.

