#### Primary and secondary objectives

To evaluate the effectiveness of the interventions, mixed-model analyses will be performed for the primary and secondary outcome measurements with time (baseline, post-intervention, follow-up) as a within subjects factor and condition (CRT vs. ETAU, MBCT vs. ETAU, and exploratory: CRT vs. MBCT) as a between-subjects factor. These analyses will be performed using an intention-to-treat approach, including all randomised participants regardless of adherence and measurement completion. Secondarily, per-protocol analyses will be performed for further exploration of the intervention effects.

To evaluate the secondary study aims, mediation and moderation analyses [61] will be performed to evaluate whether alterations in functional brain networks play a role in the effect of the interventions. In addition, cross-sectional associations between functional brain networks and cognitive function (subjective and objective) will be analysed using Pearson’s correlation and linear regression analyses. To evaluate whether alterations in secondary study parameters are mediating factors that determine subjective cognitive function, mediation analyses [61] and linear regression analyses will be performed. Finally, logistic and linear regression models will be performed to evaluate which factors determine whether a patient is likely to benefit from one of the therapies.

For all analyses, confounding variables will be inserted, such as age and education. Bonferroni corrections will be applied to correct for multiple comparisons within each objective.

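### The BRIEF-A sits under the primary outcome heading with no stated tier, so the Bonferroni rule can be read as drawing it into the CFQ's alpha

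*Protocol article*

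**What the plan says.** All references are to the protocol article.

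- **Primary outcome measure.** The section opens in the singular: "The primary outcome measure is the level of subjective cognitive complaints and is measured with the CFQ". It continues: "Subjective cognitive complaints in terms of executive function will be measured with the Behaviour Rating Inventory", and closes: "The BRIEF-A consists of a self- and an informant report version". It does not call the BRIEF-A primary, co-primary, secondary or supportive.
- **Secondary outcome measures.** The subsections cover objective cognition, functional brain networks, psychological symptoms, quality of life, well-being and daily life functioning. The BRIEF-A is in none of them. The lists of secondary outcomes in the Abstract and in Objectives have no category for subjective complaints into which it could fall.
- **Sample size calculation.** The CFQ is called the primary outcome measure and the BRIEF-A is not mentioned. The inputs are alpha .05, power .80, an intra-class correlation of .06 and 33 per group, giving a detectable difference of 0.62 SD for each of two comparisons with ETAU.
- **Objectives.** The primary aim concerns subjectively experienced cognitive problems. No instrument is named.
- **Primary and secondary objectives (Statistical analysis).** "Bonferroni corrections will be applied to correct for multiple comparisons within each objective".
- **Recruitment and consent.** The informant report is optional: "participants have the option to give permission for an informant to be contacted", and the informant then receives a separate consent form.

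**The concern.** The sentence introducing the BRIEF-A describes it in the same construct words as the primary outcome, under the same heading. Every other outcome questionnaire has a place in a secondary section. The correction for multiple testing is set per objective, and the primary objective is set by construct. Nothing in the article says which scores make up the primary family.

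Two readings stay open, and the choice could be made after the data are seen:

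- The BRIEF-A counts as a measure of the primary objective. The stated Bonferroni rule then makes the CFQ share its alpha with both BRIEF-A versions, and the CFQ is tested at a level the sample size did not allow for. A BRIEF-A effect could also be presented as a primary result.
- The BRIEF-A is supportive only. The family is then the two CFQ contrasts.

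The informant version fits the primary construct poorly. It is not the patient's own experience, and because it is optional its numbers may fall below the 33 per group assumed.

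**Working it through.** **Step 1: the plan's own figure.** For two groups, the detectable difference is (z for alpha + z for power) × √(2f/n), with n = 33 and f a variance factor.

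| Reading | f | Detectable difference |
|---|---|---|
| Two-sided .05, no ICC | 1 | 2.802 × √(2/33) = 0.690 SD |
| ICC .06 across two follow-ups | (1 + .06)/2 = .53 | 0.502 SD |
| ICC .06 across three measurements | (1 + 2 × .06)/3 = .373 | 0.421 SD |
| ICC .06 as clustering in therapy groups of 6 to 10 | 1.30 to 1.54 (both arms); 1.15 to 1.27 (one arm) | 0.79 to 0.86; 0.74 to 0.78 SD |
| One-sided .05, no ICC | 1 | 0.612 SD |
| ICC .6 across two follow-ups (assumed) | (1 + .6)/2 = .80 | 0.617 SD |

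The printed 0.62 SD does not follow from the printed ICC in any two-sided reading tried. That is a separate matter. To avoid choosing an ICC, the next step takes the stated result as given: 33 per group, 0.62 SD, 80% power at two-sided .05. The article does not state sidedness.

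**Step 2: power at a stricter alpha.** At the design point the expected test statistic is 1.960 + 0.842 = 2.802. With k tests sharing .05, power for any one of them is Φ(2.802 − z), where z is the two-sided critical value at .05/k. The detectable difference becomes 0.62 × (z + 0.842)/2.802, and the number per group becomes 33 × [(z + 0.842)/2.802]². Enrolment scales by the article's own 40/33.

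| Primary family | k | Alpha | z | Power at 0.62 SD | Detectable at 80% | Evaluable (enrolled) per group for 0.62 SD |
|---|---|---|---|---|---|---|
| As sized | 1 | .05 | 1.960 | .80 | 0.62 SD | 33 (40) |
| CFQ × two contrasts | 2 | .025 | 2.241 | Φ(0.560) = .712 | 0.68 SD | 40 (49) |
| CFQ and BRIEF-A self × two contrasts | 4 | .0125 | 2.498 | Φ(0.304) = .619 | 0.74 SD | 47 (57) |
| CFQ, BRIEF-A self and informant × two contrasts | 6 | .0083 | 2.638 | Φ(0.163) = .565 | 0.77 SD | 51 (62) |

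Of the fall from .80 to .565 (.235), .088 comes from the two CFQ contrasts alone and .147 from adding the BRIEF-A.

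**Step 3: sensitivity to the disputed input.** Power at 0.62 SD with 33 per group, as Φ(0.62/√(2f/33) − z):

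| Assumption | k = 1 | k = 2 | k = 6 |
|---|---|---|---|
| No ICC, f = 1 | .71 | .61 | .45 |
| ICC .6, two follow-ups (assumed) | .80 | .72 | .57 |
| ICC .06 as printed, two follow-ups | .93 | .89 | .79 |

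The level depends strongly on the ICC. In every row power falls from two tests to six: by .16, .15 and .09.

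**Step 4: error rate.** For six tests (three scores, two contrasts), I simulated z statistics with correlation .3 to .7 between scores and .5 between the contrasts for the shared control arm, all assumed. The chance of at least one false positive is 19% to 24% if each is tested at .05, and about 4% to 4.6% with Bonferroni over six.

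**The case against.** The strongest reply is that the article already answers the question. Two sections name the CFQ as the single primary measure and no section calls the BRIEF-A primary. Its placement can be read as grouping by construct, as Table 1 does when it puts the questionnaires on subjective complaints in one row. This is also a condensed article, and a list of the tests in each family is commonly left to the full protocol or the analysis plan.

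Much of that stands. A reader might infer that the trial has declared a primary family of three instruments. It has not: the BRIEF-A is one instrument in two versions, and what is missing is its tier. A reader might also infer a familywise error of 19% to 24%. That would require ignoring the Bonferroni rule the article states. The inflated error and the lost power are alternatives and cannot be added together. Nor does the article declare a separate primary test at each visit, so a family of twelve has no basis in the text. Finally, the sample size was not built on CFQ data: it works in SD units with an effect expected from a comparable measure.

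The reply does not remove the ambiguity. Assigning measures to tiers is what the outcome section does for the other questionnaires, and here it put a further measure of the primary construct under the primary heading. The stated rule attaches to the objective and not to the CFQ, so naming the CFQ as primary does not settle what the correction covers.

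**Conclusion.** The point holds as an ambiguity with a real consequence. The CFQ is the named primary measure, but the BRIEF-A has no tier and the stated multiplicity rule can be read to include it.

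Taking the article's design point at face value, power for a CFQ contrast at 0.62 SD is about .71 with the family limited to the two contrasts, and about .565 if both BRIEF-A versions share the alpha. Even the narrow family falls short of the stated .80, because the sample size used .05 for each comparison while the analysis section corrects for multiple comparisons.

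These figures assume two-sided tests, equal precision for all scores and a normal approximation. They rest on the stated 0.62 SD, which the printed ICC does not reproduce; with ICC .06 read across two follow-ups, the corresponding values are .89 and .79. Bonferroni is conservative for correlated scores. If fewer informant reports are returned, power for that score would be lower than shown.

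**What to change.** - In Primary outcome measure, state that the CFQ is the sole primary measure.
- Move the BRIEF-A self-report and informant report to Secondary outcome measures, under a category for subjective complaints, and add that category to the lists in the Abstract and Objectives.
- In the statistical analysis section, define the primary Bonferroni family as the two CFQ contrasts against ETAU.
- In Sample size calculation, restate the result at alpha .025: about .71 power at 0.62 SD, or 0.68 SD detectable at 80%, once the ICC behind the 0.62 SD has been confirmed.

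If the BRIEF-A is meant to be co-primary, say so, give the alpha split and resize. On the figures above, three scores by two contrasts need about 51 evaluable and 62 enrolled per group.

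The recommended route costs a few sentences and no new data. Its downsides are that a BRIEF-A effect can be reported only as secondary, and that the stated power becomes less favourable.
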